### Data monitoring

An Independent Data Monitoring Committee has been established for this study. It will meet every 3 months to review a report created by the researchers to monitor the progress of recruitment and data collection (e.g., completion rates for each follow-up).

### Ensuring the quality of therapists’ skills and sessions

Psychiatrists and clinical psychologists, licensed for at least 3 years and involved in clinical work with ASD individuals, have been engaged as cognitive-behavioral therapists for this study. The therapists for ACAT received at least 6 h of initial training on the intervention, read the treatment manual, listened to the audiotape set of the model therapist performing the treatment, and are supervised weekly by the clinical supervisor (the first author of this thesis who developed the ACAT protocol). All sessions will be recorded and evaluated by researchers unrelated to the development or operation of the ACAT program using the Cognitive Therapy Scale [32].

### ACAT program details

This study follows the ACAT protocol shown in Table 1. We started to develop a psychological education program for ASD, referring to programs for ASD outside of Japan that can be adopted as the standard in Japan.

**Table 1 Tab1:** Agenda and purpose of each ACAT session

CBT sessions	Session content	Session goals
Pre-session	Learn about your psychological assessment for ASD	The participants will learn about their personal characteristics and autistic traits through the results of assessment tests.
1st CBT	Learn about the characteristics of your autistic traits	The participants will understand the differences between autistic attributes and typical developmental features.
2nd CBT	Cognitive changes: learn not only about the “weakness” but also “strengths” of your autistic traits	The participants will discover the “strengths” of ASD, setting aside the “weaknesses” and turning negative perspectives into rational neutral understanding about themselves.
3rd CBT	Cognitive changes: create “funny nicknames” for your autistic traits	The participants will learn to externalize their autistic characteristics, facilitate self-monitoring skills, and develop metacognition.
4th CBT	Behavioral changes: create a problem-solving plan for your autistic traits	The participants will learn how they can change and adjust their problematic behaviors to cope with their autistic traits.
5th CBT	Behavioral changes: plan a functional way to solve easy problems that are caused by your autistic traits with your parents	The participants will make problem-solving plans for their own autistic traits and will also consider how to cope with problems when they execute their plans. They will start with easier problems related to their ASD traits. They will conduct these plans as a homework assignment.
6th CBT	Behavioral changes: plan a functional way to solve more complicated problems that are caused by your autistic traits with your parents	The participants will make problem-solving plans for their own autistic traits and will also consider how to manage more complicated problems when they execute their plans. They will conduct these plans as a homework assignment (this homework assignment will be checked at a follow-up session).
CBT follow-up	Check how well you are living with your autistic traits	The participants will review all skills and techniques learned to date. They will check their understanding of their own autistic traits and discuss the progress made in therapy, areas of continued effort, and ongoing challenges.

The concept of the program is to help adolescents with ASD and their caregivers learn about ASD and improve their skills in coping with “ASD traits” using CBT. The mechanism of the expected effect is that it will increase and consequently eliminate social and psychological difficulties. The ACAT protocol was preliminarily utilized in two patients with ASD and their parents to test it in clinical situations and collect feedback, after which it was revised. The ACAT program is conducted over a 100-min session per week with a 10-min break, with six sessions in total. An individual with ASD and a parent/guardian attends the session together. An agenda is prepared for each session (Table 2). The workflow is described in Table 1. The first three sessions focus on participants learning about their own ASD characteristics and their ability to externalize these characteristics by creating funny nicknames, which facilitates self-monitoring skills and development of metacognition of their characteristics. From the fourth session onward, featured difficulties (symptoms) arising from their autistic traits are discussed. These procedures reasonably accommodate the individual abilities of each participant. Each session has a homework assignment that focuses on reviewing the discussed material. If a participant forgets to do a homework assignment or is absent or late to a session for any reason, a make-up session will be provided to fill in the gaps.

**Table 2 Tab2:** Agenda for each session

Minutes (total 100)	Contents of each session
10	Check the condition and mood over the week (0–100 evaluation) based on the ACAT textbook
20	Check homework assignments
20	Read the ACAT textbook related to the day’s topic (about the day’s topic, see Table 1)
10	Break
30	Practice work (e.g., cognitive and behavioral intervention) related to the day’s topic based on the ACAT textbook
5	Set homework assignment that is related to the day’s topic
5	Ask the patient and parent for feedback about the session

### Schedule for screening tests

Table 3 describes the operational schedule for the screening test and outcome measures.

**Table 3 Tab3:** Standard Protocol Items: Recommendations for Interventional Trials (SPIRIT) diagram

Time point**	Study period							
	Enrollment, ***May 2017***_***1***_	Allocation, March 2018	Post-allocation					Close-out, ***May 2020***
			***0w***	***6w***	***10w***	***t***_***4***_	etc.	
**Enrollment:**								
**Eligibility screen**	X							
**Informed consent**	X							
**Allocation**		X						
**Interventions:**								
***Combination (ACAT) group***			X	X	X			
***TAU group***			X	X	X			
**Assessments:**								
***Socioeconomic and demographic data***	X	X	X	X	X			
***Patients: AKQ-C, DSRS-C, BACEv3, EEG***	X	X	X	X	X			
***Parents: AKQ-P, SDQ, Vineland-2, Bace-v3, GHQ-12, EEG***	X	X	X	X	X			

*AKQ-C* Autism Knowledge Quiz-Child, *DSRS-C* Depression Self-Rating Scale for Children, *BACEv3* Barriers to Access to Care Evaluation scale version 3, *EEG* electroencephalogram, *AKQ-P* Autism Knowledge Quiz-Parents, *SDQ* Strengths and Difficulties Questionnaire, *GHQ-12* General Health Questionnaire

Screening tests will be conducted for participants and their parents after obtaining their informed consent. A physician or therapist will perform the screening tests as shown in Table 3. Patients who qualify according to the selection criteria and do not meet the exclusion criteria will be selected. As inspection items, we will ascertain the backgrounds and names of participants and dosage of psychotropic drugs administered to them along with their usage period. We will conduct the Autism Diagnostic Observation Schedule Second Edition (ADOS-2) [27] and Autism Diagnostic Interview-Revised (ADI-R) [28] to assess ASD and the ADHD Rating Scale-IV (ADHD-RS) [33] to assess hyperactivity and impulsivity accompanying their ASD. We will conduct the Japanese version of the Sensory Profile [34] to assess dysesthesia and administer the Strengths and Difficulties Questionnaire (SDQ) [30] to assess behavioral problems. We will also conduct the Wechsler Adult Intelligence Scale-III (WAIS-III) or Wechsler Intelligence Scale for Children, Fourth Edition (WISC-IV) [35] according to the patient’s age to assess their intelligence level. Further, the Mini International Neuropsychiatric Interview (M.I.N.I.) [31] will be used to screen the parents of participating patients for the presence of diagnostic criteria, including panic disorder, agoraphobia, general anxiety, and depression.

### Outcome measures

#### Primary outcomes

##### Autism Knowledge Quiz-Child (AKQ-C)

AKQ-C [17] has two sections, namely, a five-item structured interview on “awareness of autistic characteristics” and a 15-item knowledge quiz. The main evaluation items of this study include variations in the “awareness of autistic characteristics” measured in section 1 of the AKQ-C, which will be administered during the pre-intervention, post-intervention, and follow-up period.

#### Secondary outcomes

##### Depression Self-Rating Scale for Children (DSRS-C)

DSRS-C [36] is a self-assessment scale containing 18 items. It assesses the level of depression among children by enquiring about their feelings over a week; each item is marked on a three-point scale: “always,” “sometimes,” and “never.” This scale will be applied to children/adolescents at three different time points: pre-intervention, post-intervention, and follow-up.

##### Barriers to Access to Care Evaluation scale version 3 (BACE-3)

The BACE [37] is a 30-item questionnaire designed to assess the barriers to mental health care for people with mental health problems. It includes barriers related and unrelated to stigma and discrimination. This scale will be applied to both children/adolescents and parents/guardians at three different time points: pre-intervention, post-intervention, and follow-up.

##### Strengths and Difficulties Questionnaire (SDQ)

SDQ [30] is a short screening instrument that addresses the positive and negative behavioral attributes of infants, children, and adolescents. It includes 25 items, and each item can be marked “not true,” “somewhat true,” or “certainly true.” The scale will be applied to parents/guardians who are requested to score their children/adolescents at three different time points: pre-intervention, post-intervention, and follow-up.

##### Vineland Adaptive Behavior Scales second edition (Vineland-2)

Vineland-2 [38] is a semi-structured interview for parents to capture the developmental norm of adaptive behavior in individuals aged 0–92 years. Interviews will be conducted with parents/guardians about their children at three different time points: pre-intervention, post-intervention, and follow-up.

##### Autism Knowledge Quiz-Parents (AKQ-P) (for parents/guardians)

AKQ-P [17] is the parent version of AKQ-C. We will apply this scale to parents/guardians at three different time points: pre-intervention, post-intervention, and follow-up.

##### The 12-item General Health Questionnaire (GHQ12) (for parents/guardians)

GHQ [39] is a measure of current mental health. The questionnaire was originally developed as a 60-item instrument; however, a range of shortened versions of the questionnaire such as GHQ-30, GHQ-28, GHQ-20, and GHQ-12 are available. The scale tests if respondents recently experienced a particular symptom or behavior. Each item is rated on a 4-point scale (less than usual, no more than usual, rather more than usual, or much more than usual); for GHQ-12, it gives a total score of 36 or 12 based on the selected scoring methods. We will apply this scale to parents/guardians at three different time points: pre-intervention, post-intervention, and follow-up.

##### Parenting Resilience Elements Questionnaire (PREQ) (for parents/guardians)

PREQ [40] measures the degree to which mothers possess elements that aid in adapting to challenges and difficulties related to children with developmental disorders. It comprises 29 items and three factors, namely, “knowledge of the child’s characteristics,” “perceived social supports,” and “positive perceptions of parenting.” Each item is scored on a 7-point Likert scale from 1 (strongly disagree) to 7 (strongly agree). We will apply this scale to parents/guardians at three different time points: pre-intervention, post-intervention, and follow-up.

##### Electroencephalogram (EEG)

An EEG analysis can be used to detect the disrupted functions of large-scale cortical activity in ASD patients and to provide objective indices to evaluate the effectiveness of this program [41]. Therefore, resting-state EEG will be recorded as an objective physiological index alongside the questionnaire. The EEG scale will be applied to both children/adolescents and parents/guardians at three different time points: pre-intervention, post-intervention, and follow-up.

### Other measurements

Before and after treatment, parents are requested to report their children’s current medication, dose of medication, and outpatient (hospital) care.

### Sample size

The sample size was calculated using the G*power software version 3.1.9.2 with a power of 0.80 and *α* = 0.05 (two-tailed). In a previous study [17], the change in AKQ’s “ASD awareness” was 2.26, and the effect size was 0.92. Considering a drop out ratio of 20%, the ideal sample size was estimated as 48.

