**Methods:**

This multisite study is a randomized controlled trial. In total, 24 participants will be assigned to the ACAT group and 24 to the treatment-as-usual (TAU) group. The ACAT group will receive a weekly 100-min session for 6 weeks, regular medical care, and one follow-up session. In this ongoing clinical trial, we will compare the scores of the measures recorded in the pre- and post-intervention stages between the ACAT and TAU groups. A total of 41 patients out of a target of 48 have participated in the trial to date. The primary outcome measure is the Autism Knowledge Questionnaire. Secondary outcome measures include Barriers to Access to Care Evaluation 3rd Edition, the Strengths and Difficulties Questionnaire, the Vineland Adaptive Behavior Scales second edition, the Parenting Resilience Elements Questionnaire, the General Health Questionnaire 12, and the Depression Self-Rating Scale for Children assessments, as well as an electroencephalographic recording.

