### Randomization and blinding

Enrollment and randomization are based on the central registration system of the Clinical Research Data Center at Chiba University Hospital, Chiba, Japan. Two allocation factors are used for stratification: the degree of knowledge (high or low) regarding the characteristics of ASD according to the primary outcome measure, the Autism Knowledge Quiz-Child (AKQ-C), and gender (male or female). At the end of the baseline assessment, eligible participants will be randomly assigned to either the TAU arm or ACAT plus TAU arm at a ratio of 1:1, with assignments made using the minimization method, ensuring a balance across baseline AKQ scores and gender. Each participant will then be assigned to one of the two treatments. Participants will not be blinded to the group to which they are assigned before consenting to participate in the study. However, trained testers, who will assess all outcome measures except the self-assessment scale, will be blinded to the group.

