### Statistical methods

#### Statistical analysis plan

We are currently collecting data from 41 of 48 child/adolescent ASD patients and their parents/guardians. Treatments will end during the spring of 2020, and analysis of the data will commence in the summer of 2020. The purpose of this study is to examine the relative efficacy of ACAT for child/adolescent ASD patients and their parents/guardians, in terms of ASD awareness scores, compared to the TAU group. Therefore, the primary analysis will evaluate the differences in score variations (i.e., the ACAT and TAU groups’ mean variations) for ASD awareness from week 0 (baseline) to week 6. Relative efficacy will be indicated when the point estimate of mean variation difference has a positive value and when the value of the ACAT group statistically exceeds that of the TAU group. The examination of scores will be based on an analysis of covariance (ANCOVA) for interval estimation of mean variation differences and calculation of the P value using allocation factors as adjustment factors (gender and AKQ-C score). The secondary evaluation of efficacy items will supplement the main results of the analysis, and redundancy will not be adjusted. The level of significance for the hypothesis test is 5% on two sides, with a two-sided confidence interval of 95%.

The results of the BACE-3, AKQ-P, SDQ, Vineland-2, DSRS-C, PREQ, and GHQ-12 (self-completed by parents) will be analyzed using the same techniques used for the assessment of the main evaluation items. In addition, EEG of individuals with HF-ASD as well as their parents/guardians will be recorded at pre-intervention, post-intervention, and follow-up to investigate neurological changes. EEG signals will be registered with a 19-channel box of Mitsar-EEG 201 (Mitsar Co. Ltd.). The 19-channel EEG cap will be fitted in accordance with a standard 10–20 system. EEG analysis will be conducted based on graph theory. The overall efficiency, clustering coefficients, connection between the left and right hemispheres, and network resilience will be calculated and compared between the ACAT and TAU groups.

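### At 20% dropout, the G*Power t-test inputs lead to 50 randomised participants rather than 48; unadjusted power at 48 is about 79% (minor)

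*Protocol article*

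**What the plan says.** The Sample size section of the protocol article identifies the tool and the target ("The sample size was calculated using the G*power software version 3.1.9.2 with a power of 0.80"), sets alpha at 0.05 two-tailed, and takes its effect from an earlier study of a psychoeducation programme, where "the effect size was 0.92". It concludes: "Considering a drop out ratio of 20%, the ideal sample size was estimated as 48".

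The other design inputs appear elsewhere in the article:

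- The Abstract (Methods) gives the split: "24 participants will be assigned to the ACAT group and 24 to the treatment-as-usual (TAU) group".
- Randomization and blinding sets the allocation ratio at 1:1.
- The Statistical analysis plan section confirms the test level: "The level of significance for the hypothesis test is 5% on two sides". It also specifies the primary analysis as an ANCOVA of change in ASD awareness from week 0 to week 6, adjusted for gender and AKQ-C score.

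The article does not state the number needed before dropout, the test selected in G*Power, the type of effect size that 0.92 represents, or how the 20% was applied.

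**The concern.** A sample size that allows for dropout should leave the required number of evaluable participants once the assumed fraction is lost. That means dividing the evaluable number by one minus the dropout proportion. Multiplying by one plus the proportion is a common slip and always falls short. Here the stated inputs give 40 evaluable participants with the t-test, and 48 is exactly 20% more than 40.

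What is at stake is whether sample size, dropout allowance and power agree with one another in a statement that the results report is likely to repeat. The conduct of the trial is not in question.

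**Working it through.** **Inputs.** Effect size 0.92, power 0.80, two-sided alpha 0.05 and dropout 20% (Sample size); 1:1 allocation (Randomization and blinding); 24 + 24 (Abstract, Methods). One assumption is needed: 0.92 is taken as a between-group standardised difference d, since the article does not name its type.

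**Step 1: evaluable number, two-sample t-test.** This is G*Power's calculation for two independent means. With n per arm, df = 2n − 2 and the noncentrality is d × √(n/2). Power is the probability that a noncentral t variable falls beyond the two-sided 5% critical value.

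| n per arm | Total | Noncentrality | Power |
|---|---|---|---|
| 19 | 38 | 0.92 × √9.5 = 2.836 | 0.788 |
| 20 | 40 | 0.92 × √10 = 2.909 | 0.809 |

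The smallest equal-arm size that reaches 0.80 is 20 per arm, 40 in total.

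**Step 2: reproducing 48.** Two routes lead to the stated figure.

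- t-test number multiplied up: 40 × 1.2 = 48.
- Normal-approximation number divided correctly: n = 2 × (1.960 + 0.842)² / 0.92² = 18.55, rounded up to 19 per arm, or 38. Then 38/0.8 = 47.5, rounded up to 48.

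The article does not say which route was used, if either.

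**Step 3: dropout allowance applied to the t-test number.** 40 / (1 − 0.20) = 50, or 25 per arm.

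**Step 4: what 48 delivers.**

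- Expected completers at 20% loss: 48 × 0.80 = 38.4, fewer than 40.
- Dropout at which 40 remain: 1 − 40/48 = 16.7%.
- Unadjusted t-test power at 19 + 19: 0.788. At 19 + 20: 0.799. Averaged over binomial dropout of 20% in each arm: 0.788.
- Difference detectable with 80% power at 19 per arm: d = 0.934, against the planned 0.92.

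The shortfall is at most about 0.80 − 0.788 = 0.012, or 1.2 percentage points.

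**Step 5: the planned ANCOVA.** Let r be the correlation of the covariates with the change score within arms. The article gives no value, so a range is shown. The effective difference becomes 0.92/√(1 − r²), with df = 2n − 4 because two covariates are fitted. At 19 per arm:

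| r | Power |
|---|---|
| 0 | 0.787 |
| 0.2 | 0.803 |
| 0.3 | 0.823 |

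Power crosses 0.80 at r of about 0.18, where the covariates explain about 3.3% of the variance in change.

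**The case against.** The strongest reply is that nothing is demonstrably wrong. The article prints neither 40 nor a factor of 1.2, and 48 follows from correct division if the evaluable number came from a normal approximation. The primary analysis is also a covariate-adjusted ANCOVA rather than the unadjusted t-test, and a weak covariate correlation restores 80% power. Finally, the gap of two participants and about one point of power is trivial beside the uncertainty of an effect size borrowed from one earlier study.

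Much of this stands. A reader might infer that the sponsor is known to have multiplied by 1.2. The document does not support that: the mechanism is an inference. It is the likelier one because G*Power is named and its two-means t-test gives 40. A reader might also infer that the design fails its power target. That is not supported either, because the only shortfall shown is about one point, for an unadjusted comparison that is not the planned primary analysis.

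Two parts of the reply do not remove the point. The normal approximation is slightly optimistic at this size: its 38 completers have t-test power of 0.788, so by either route 48 with 20% loss falls just below 0.80 unadjusted. And the Sample size section claims no gain from covariates and states no correlation, so the ANCOVA cannot be the basis of the printed calculation, even though it may well make good the difference in practice.

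**Conclusion.** Minor, but wrong as written. With 0.92 read as a between-group standardised difference and the t-test of the named software, the stated inputs require 40 evaluable and 50 randomised participants at 20% dropout. The stated 48 matches a dropout allowance of 16.7%, or unadjusted power of about 79% at 20% dropout.

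The conclusion depends on that reading of 0.92 and on an unadjusted two-sample t-test as the basis of the calculation. It is a mismatch between three printed figures and does not show that the trial is underpowered. Whether the planned ANCOVA reaches 80% at 20% dropout depends on a correlation that the article does not give; about 0.18 would be enough.

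**What to change.** Leave enrolment at 48 and correct the statement, along these lines: 48 randomised participants (24 per arm) give 80% power for d = 0.92 at two-sided 0.05 with up to 16.7% dropout (40 evaluable); at 20% dropout (about 38 evaluable), power for an unadjusted comparison is about 79%. Add that the planned baseline-adjusted ANCOVA is expected to reach 80% at 20% dropout if its covariates correlate at about 0.18 or more with the change score, and label this as an assumption. In the same place, give the evaluable number before dropout, the rule used to inflate it, and the type of effect size.

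The cost is a sentence or two and a slightly less favourable unadjusted power figure. Recruitment, allocation, endpoints and analysis are unchanged. The corrected wording should be used wherever the sample size justification is repeated, in particular in the results report.
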